## Abstract

**Background:**

Patients with pre-existing impaired renal function are prone to develop acute contrast media induced nephropathy (CIN). Neutrophil gelatinase-associated lipocalin (NGAL), a new biomarker predictive for acute kidney injury (AKI), has been shown to be useful for earlier diagnosis of CIN; however, urinary NGAL values may be markedly increased in chronic renal failure at baseline. Results from those studies suggested that urinary NGAL values may not be helpful for the clinician. An intravenous volume load is a widely accepted prophylactic measure and possibly a reasonable intervention to prevent deterioration of renal function. The aim of our study is to evaluate NGAL as an early predictor of CIN and to investigate the clinical benefit of early post-procedural i.v. hydration.

**Methods/Design:**

The study will follow a prospective, open-label, randomized controlled design. Patients requiring intra-arterial contrast media (CM) application will be included and receive standardized, weight-based, intravenous hydration before investigation. Subjects with markedly increased urinary NGAL values after CM application will be randomized into one of two study groups. Group A will receive 3-4 ml/kg BW/h 0.9% saline intravenously for 6 hours. Group B will undergo only standard treatment consisting of unrestricted oral fluid intake. The primary outcome measure will be CIN defined by an increase greater than 25% of baseline serum creatinine. Secondary outcomes will include urinary NGAL values, cystatin C values, contrast media associated changes in cardiac parameters such as NT-pro-BNP/troponin T, changes in urinary cytology, need for renal replacement treatment, length of stay in hospital and death.

We assume that 20% of the included patients will show a definite rise in urinary NGAL. Prospective statistical power calculations indicate that the study will have 80% statistical power to detect a clinically significant decrease of CIN of 40% in the treatment arm if 1200 patients are recruited into the study.

**Discussion:**

A volume expansion strategy showing a benefit from earlier intervention for patients with markedly elevated urinary NGAL values, indicating a CIN, might arise from data from this study.

**Trial registration:**

ClinicalTrials.gov NCT01292317

## Background

In recent decades, the growing demand for sophisticated diagnostics in all fields of modern medicine has increased the need for contrast-enhanced imaging [1]. The amount of iodinated contrast media (CM) used worldwide cannot be even roughly estimated. While contrast-enhanced procedures are fairly safe in the healthy population, patients with pre-existing impaired renal and/or cardiac function are prone to develop acute kidney injury (AKI) due to acute contrast induced nephropathy (CIN) and so have a greater risk of death [2,3]. This has been shown in patients undergoing coronary angiography and intervention who sometimes end up with end-stage renal disease [4,5]. The effect of an immediate post-procedural hemodialysis treatment to eliminate CM load is also discussed controversially [6,7].

Until recently and for this reason, physicians have increasingly used gadolinium enhanced magnetic resonance imaging to avoid renal complications, especially in such high-risk patients. For interventional settings, however, gadolinium enhanced magnetic resonance imaging has never been an appropriate alternative.

Also, with the recognition of nephrogenic systemic sclerosis as a severe and also life-threatening gadolinium side effect without treatment options, physicians now have to weigh the risk of either investigation for the individual patient [8,9]. A return to iodinated CM enhanced investigations is now seen in many clinical settings.

A variety of investigators have tried to establish risk scores for patients before investigation [10,11]. To date, a reliable laboratory value or test that recognizes acute renal damage before serum creatinine increases is still being sought and might be a most helpful tool to initiate proper treatment on time. Neutrophil gelatinase-associated lipocalin (NGAL), a new biomarker predictive for acute renal injury, has been shown to be capable of earlier diagnosis in patients undergoing cardiac surgery and CIN [12-16]. NGAL so might be the desired diagnostic link between acute kidney damage and the later occurrence of elevated creatinine values. Randomized controlled trials using this "timesaver" for earlier intervention have not yet been performed, but would be highly desirable [17]. Such a study might change physicians' therapeutic strategies and improve clinical outcomes.

One major drawback of this new biomarker may be the fact that only little is known about its value and accuracy in patients with underlying chronic kidney disease (CKD), and a predictive pattern or cut-off level in patients developing "acute on chronic renal failure" has not yet been defined. Some investigators found markedly increased NGAL levels in individual patients, far above the proposed cut-offs for acute renal failure. They also discovered a significant inverse relation between NGAL and renal function defined by glomerular filtration rate (GFR) [18,19]. Mori et al. have speculated that constantly increased, yet stable NGAL values in CKD are the consequences of sustained production by "inflamed", but vital tubular cells [20]. Even more complicating is the fact that age and several co-morbidities, such as inflammation and chronic heart disease, common in patients with chronic renal failure, may also influence NGAL levels [21,22]. A meta-analysis by Haase et al. selected 19 relevant published articles and defined 150 ng/ml as a possible cut-off value with a proper sensitivity and specificity [23]. This analysis also confirmed a comparable accuracy of plasma and urinary NGAL, whereas urinary NGAL testing may be even better in patients with CKD [24].

So far, an intravenous volume load is the only reasonably proven and widely accepted prophylaxis for CIN after CM application [25-28]. In the majority of the relevant randomized controlled trials, isotonic saline infusion (0.9%) was used for volume expansion, while some authors used half-isotonic saline (0.45%) or sodium bicarbonate at higher volumes. The benefit of this type of intervention is not a pharmacologic effect of a specific type of infusion, but rather a physical effect of volume expansion. The optimal intravenous fluid regimen regarding the type, amount, route and duration of volume application remains controversial.

Hydration regimens have differed widely among relevant randomized trials and so are not comparable [29]. Further, most studies also lacked statistical power, used different types of CM and definitions of CIN or allowed for additional prophylactic measures, such as N-acetylcysteine or sodium bicarbonate in a varying percentage of their patients [30-38].

Worldwide, there are no generally accepted guidelines for a controlled and standardized prophylactic volume application among radiologists, cardiologists, nephrologists and other involved physicians. In other words, the beneficial effect of intravenous hydration is not used to greatest advantage.

In our study, all patients requiring intra-arterial CM application will receive a weight-based, standardized intravenous hydration before investigation. This measure of controlled pre-hydration alone might be of great benefit for our patients and differs from routine clinical practice, where patients often only receive oral fluid at best. To date, intravenous hydration is not even an established clinical standard for the so-called "high-risk patient" with e.g. diabetes and/or renal failure.

A randomized trial evaluating the clinical benefit of additional post-procedural i.v. hydration might provide a further benefit and could be highly valuable for routine practice.

Controlled post-procedural i.v. hydration has not been used consistently for several reasons [29]:

(a) worldwide, a large percentage of CM studies are performed on an outpatient basis;

(b) there are no clear data proving the benefit of additional post-procedural i.v. hydration, versus pre-procedural hydration only;

(c) intravenous hydration, both pre- and post-procedural, is often not performed for organizational reasons.

### Rationale and hypothesis

Earlier detection of CIN by the novel urinary NGAL test method enables amelioration of renal injury by the introduction of rapid and intensified post-procedural (angiography) volume expansion.

### Aims of our study

1). To evaluate the true risk of CIN in high-risk patients following intra-arterial angiography using a standardized pre-procedural protocol for intravenous volume load.

2). To evaluate the benefit of an earlier diagnosis of renal damage after investigation using urinary NGAL.

3). To investigate the effect of a well-timed and intensified post-procedural volume expansion on renal function, morbidity and mortality in patients predicted to develop CIN according to NGAL testing.

4). To study NGAL in patients with mild, moderate and severe CKD (stage 2-4), a subgroup of individuals who frequently develop CIN. At present it is still unclear whether the new biomarker NGAL is comparably effective in this particular group.

5). To define and establish a reliable cut-off value or pattern of increase for NGAL in patients with chronic renal failure and to estimate its sensitivity and specificity.

6). To assess the value of a 25% increase in serum creatinine as a definition for clinically relevant CIN.

7). To compare the value of NGAL and cystatin C in predicting CIN.

8). To compare the value of the MDRD, the CKD-EPI- and the Cockcroft-Gault formula in this particular patient group.

At this stage, little is known about the beneficial effect of earlier diagnosis and subsequent intervention by volume expansion on AKI due to a rise in urinary NGAL. As the time course of kidney damage is usually not apparent, contrast media induced nephropathy (CIN) is a promising condition for this question. Results from previous studies are unable to guide the clinician when baseline urinary NGAL levels exceed the normal range.

To our knowledge, this is the first clinical study to address this problem. We are trying to assess the effect of an early intervention by volume expansion in patients with increasing urinary NGAL levels 4-6 hours following CM application. If a significant reduction of CIN as defined by creatinine levels is found in the treatment arm within 2 days, a clear benefit of measuring urinary NGAL might be postulated. We are currently recruiting patients for this non-commercial investigator initiated trial to elucidate CIN.

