### Sample size calculations

Sample Size: Alpha = 0.05, power = 0.8, two-sided test. Assuming a clinically relevant difference in CIN incidence of 20% and 60% CIN in the control group (worst case), 108 patients per group are required for the chi square test. Only patients who meet the NGAL criteria for randomization will be included. We assume that 20% of the included patients, which would amount to about 1200 patients, will be randomized to treatment groups. If fewer than 48 patients are randomized after the inclusion of 240 patients, the NGAL criteria for randomization will be adapted in order to meet the objective of including not more than 1200 patients. Recruitment will continue until 240 patients have been randomized.

Analysis: Chi square tests will be used for CIN reduction. Wilcoxon's rank sum test will be applied to continuous measurements.

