### Statistical considerations

The diagnostic value of a two-point-measurement of NGAL, cystatin C and creatinine before and after CM application, as compared to a single-point-measurement only after CM application with respect to CIN will be assessed through receiver operating characteristic (ROC) within the patients who received standard therapy. The analysis has to account for the bias that is caused by the exclusion of patients who receive treatment A from ROC analysis on the condition of an elevated NGAL. The available sample size for ROC analysis is determined by the number of patients, the incidence of CIN and the number of patients who receive treatment A. We assume that 20% of the included patients will develop CIN.

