### Data analysis

Treatments will be compared according to relative change of creatinine from baseline by the Wilcoxon test and Pearson's chi square test (two-sided, alpha = 0.05).

As mentioned above, those patients without a relevant increase of NGAL will also be followed. This will allow us to retrospectively calculate sensitivity and specificity of NGAL testing for CIN.

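### Aim 5 derives an NGAL cut-off and estimates its accuracy in the same patients; the resulting optimism is small (about 3 points) and cheap to correct

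*Protocol article*

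**What the plan says.** Under Aims of our study, aim 5 reads "To define and establish a reliable cut-off value or pattern of increase for NGAL in patients with chronic renal failure and to estimate" that rule's sensitivity and specificity. Deriving the rule and judging it therefore form one aim of one single-centre study.

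Under Statistical considerations, the diagnostic value of two-point against single-point measurement "will be assessed through receiver operating characteristic (ROC) within the patients who received standard therapy". That section gives no number for this set, only its determinants, the last being the size of Group A: "The available sample size for ROC analysis is determined by the number of patients, the incidence of CIN and the number of patients who receive" … It names one bias to be accounted for, the removal of Group A patients on the condition of a raised NGAL.

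Under Data analysis, patients without a relevant NGAL rise are also followed: "This will allow us to retrospectively calculate sensitivity and specificity of NGAL testing for CIN".

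The thresholds for randomisation are set in advance from cited sources, under Randomization: above 150 ng/ml if baseline is below 75 ng/ml, or a doubling if baseline is above 75 ng/ml. Sample size calculations allows these criteria to be adapted if fewer than 48 of the first 240 patients are randomised. Discussion item 4 mentions tuning the cut-off after an intermediate analysis.

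**The concern.** When a cut-off is picked because it separates cases from non-cases best in a sample, part of its apparent performance is chance. The sensitivity and specificity read off the same sample are then apparent values, biased upward. Aim 5 also leaves the form of the rule open (a value or a pattern of increase), and choosing among several forms adds to the effect.

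The Background says that no cut-off has been defined for acute-on-chronic renal failure, so a threshold reported from this trial could be taken up with little to compare it against. The error falls mainly on sensitivity, which determines how many CIN cases the rule would miss.

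**Working it through.** **The plan's own figures.** The article gives no figure for diagnostic accuracy. Its only computed sample size belongs to the treatment comparison ("Alpha = 0.05, power = 0.8, two-sided test", 60% against 40% CIN, 108 per group):

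- Without continuity correction: (1.96·√(2·0.5·0.5) + 0.84·√(0.24 + 0.24))² / 0.20² = 97.
- With continuity correction: (97/4)·(1 + √(1 + 4/(97·0.20)))² = 107, which reproduces the stated 108 to within one patient.

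That figure does not bear on this point.

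**Size of the ROC set.** Inputs: "We assume that 20% of the included patients, which would amount to about 1200 patients, will be randomized to treatment groups"; "Recruitment will continue until 240 patients have been randomized"; "We assume that 20% of the included patients will develop CIN"; and 60% CIN in the control group (Sample size calculations).

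- NGAL-positive: 0.20 × 1200 = 240, so about 120 per group.
- ROC set without Group A: 1200 − 120 = 1080.
- CIN in all patients: 0.20 × 1200 = 240. Among NGAL-positive: 0.60 × 240 = 144. Among NGAL-negative: 240 − 144 = 96.
- CIN in the ROC set: 0.60 × 120 + 96 = 72 + 96 = 168. Non-CIN: 1080 − 168 = 912.

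If the 60% were 40%, the CIN count would be 48 + 144 = 192. If it were 80%, it would be 96 + 48 = 144. The order of magnitude does not depend on that input.

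**Plausible AUC.** The same counts imply, for the randomisation criteria, sensitivity 144/240 = 0.60 and specificity 1 − (240 − 144)/960 = 0.90. With an equal-variance binormal marker, AUC = Φ((0.253 + 1.282)/√2) = 0.86. The article gives no AUC, so I took a range of 0.70 to 0.86.

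**Optimism.** In each of 3000 simulated samples of 168 CIN and 912 non-CIN patients, the cut-off maximising sensitivity + specificity − 1 (Youden) was chosen. Its accuracy in the sample was then compared with its true accuracy.

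| AUC | Sensitivity, apparent / true | Specificity, apparent / true | Overstatement of the sum (points) |
|---|---|---|---|
| 0.70 | 0.661 / 0.632 | 0.653 / 0.649 | 3.4 |
| 0.80 | 0.739 / 0.714 | 0.731 / 0.727 | 2.9 |
| 0.86 | 0.791 / 0.769 | 0.782 / 0.779 | 2.5 |

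Sensitivity carries 2.2 to 2.9 points of this and specificity 0.3 to 0.5. With 240 CIN and 960 non-CIN patients, the whole cohort, the overstatement of the sum is 2.2 to 2.8 points.

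**Scale.** The standard error of a sensitivity of 0.60 from 168 cases is √(0.60 × 0.40/168) = 0.038, or 3.8 points. The optimism is below one standard error.

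**The case against.** The strongest reply is that aim 5 states an objective, not an estimator. The article names no rule for choosing the cut-off and does not say that accuracy will go uncorrected. A condensed article may leave internal validation to a fuller document. This stands as a limit on the point: what the text fixes is one study population for both tasks, with no validation set described. It does not show that correction has been ruled out.

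Three stronger readings are tempting, and the article does not support them.

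- *That the bias is worst within CKD stages.* A reader might infer this from aim 4, but that aim only says NGAL will be studied in stages 2 to 4, and aim 5 treats chronic renal failure as a whole. No stage-specific cut-off is planned and no split by stage is given. If one were derived in a stage holding a third of the set (56 CIN, 304 non-CIN, an assumed share), the overstatement would be 5.0 to 6.5 points. That is conditional on something the article does not say.
- *That the calculation under Data analysis is optimistic.* Following patients without a relevant rise most naturally completes the table for the pre-set randomisation rule. That rule was not chosen on these data and carries no such optimism unless it is adapted on them.
- *That the reported accuracy will be too high on balance.* Leaving Group A out without adjustment would lower the pre-set rule's sensitivity from 144/240 = 60% to 72/168 = 43%, about 17 points the other way. The article already says that this must be accounted for. Selection optimism is a separate and smaller component, and it remains after that adjustment.

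**Conclusion.** The point holds in a limited form. Following aim 5 as written gives apparent accuracy for a newly derived cut-off or pattern, overstating sensitivity plus specificity by about 2.5 to 3.4 points, mostly in sensitivity. The direction is known, but the size is less than one standard error, so the bias alone would not make a weak rule look reliable.

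The figure rests on the article's planning assumptions (1200 included, 240 randomised, 20% CIN overall, 60% in controls) and on mine: an equal-variance binormal marker, AUC 0.70 to 0.86, a Youden-type cut-off, a search over one threshold only, and no modelling of the Group A exclusion. A search over several patterns would add to it by an amount not quantified here. The primary outcome, the randomised comparison and the sample size are untouched. This is a worthwhile refinement of a secondary aim, not a flaw in the trial.

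**What to change.** For any cut-off or pattern newly derived from this trial:

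1. Label it exploratory.
2. Report bootstrap optimism-corrected sensitivity and specificity. In each resample, repeat the whole search over cut-offs and patterns, together with the adjustment for leaving out Group A that Statistical considerations already requires.
3. Report the pre-set rule under Randomization (above 150 ng/ml, or doubling) separately as the unselected benchmark, provided it has not been adapted on trial data. If it has been, say so.

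This needs a little analysis code and yields slightly less favourable accuracy figures. It needs no further patients and no change to trial conduct or to the primary analysis.

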## Methods and design

### Study Design and Setting

This study is a single center, open label, randomized controlled trial involving subjects undergoing an intra-arterial angiographic procedure with iodinated CM. The study is being conducted at the University Hospital in Graz, Austria.

### Ethical considerations

The Ethics Committee of the Medical University of Graz, Austria, approved this trial (Registration Number: 21-278 ex 09/10). The Ethics Committees will be provided with annual reports of trial progress and will promptly receive all adverse event reports. Participants may declare their withdrawal at any time during the study.

### Participants

Patients scheduled for diagnostic intra-arterial catheter angiography or endovascular intervention will be invited to participate in the study. Only one type of iso-osmolar, non-ionic, monomeric CM (Iomeron^®^) will be used. The most common underlying diseases in these individuals are coronary heart disease, peripheral arterial occlusive disease and renal artery stenosis.

### Identification of eligible patients

The principle investigator and the clinical trial coordinators will screen the medical records of patients for pre-existing renal failure one day prior to an angiographic intervention at the Divisions of Nephrology, Cardiology, Angiology and Radiology at the University Hospital in Graz, Austria. Eligible patients will have a copy of the patient information sheet placed in the medical record. The investigator will explain the study during the clinical consultation. Only subjects giving written informed consent will be included. The study period will last 4 days, starting one day prior to investigation and ending two days after the intra-arterial angiography (Figure 1). A one year follow up consultation is targeted. All patients with CIN will be followed separately.

**Figure 1 F1:**
[figure not shown]
**Scheme for ANTI-CIN Study**.

### Inclusion criteria

• Patients requiring intra-arterial angiography/angioplasty

• Patients older than 18 years

• Patients with clinically stable CKD of stage 2 or more (calculated GFR < 70 ml/min/1,73 m2)(65)

• Gender: both

• Written informed consent

### Exclusion criteria

• Pre-existing clinical and/or laboratory evidence of acute renal failure at the time of enrolment

• Evidence of rhabdomyolysis

• Patients on renal replacement therapy (34)

• Patients with life-threatening underlying disease

• Contraindication for volume therapy

• Pregnancy

• CM application within 7 days prior to intervention

### Standardized procedure

Hospitalized patients scheduled for elective intra-arterial angiography will be prepared for CM application using a weight-based hydration protocol.

Monomeric Iomeron^® ^(iomeprol, Bracco Austria, Vienna) will be used exclusively as contrast media. Blood samples for standard evaluation, including serum creatinine and cystatin C, will be drawn at baseline and after 24 and 48 hours from all patients. A BW/h saline infusion (3-5 ml/kg) will be given for 3 hours before CM application. Urine samples for NGAL testing will be collected shortly before (baseline) and after 4 to 6 hours following CM application. NGAL will be measured with the commercially available ARCHITECT^® ^NGAL Test, Abbott Laboratories, Abbott Park, Illinois, U.S.A. [15,39].

Patients who develop CIN will be treated and followed at the Division of Nephrology and Hemodialysis according to established standards.

